## **10.Data Collection Forms, Data Management**

### **Data Collection Forms**

All the relevant patient data for the study will be recorded in anonymous format on a Case Report Form (CRF). The following data will be documented: The patient's randomisation number study-specific procedures (administration of the investigational drug, serum sampling), inclusion and exclusion criteria, demographic data, medical history and concomitant treatments, findings copied from the patient's file, follow-up observation of the period of ventilation and the planned length of stay.

Data will be entered on-line via a protected access to a data bank hosted at the CTU Zurich. Plausibility checks will be performed continuously and data entry will be checked by a monitor. Query forms integrated in the data management software will be used to explain and correct with the investigating physician.

### **How will individual findings be collected and documented?**

Data will be entered on-line from the patients' files (original data, source data) in each participating center. The following data will be collected on the basis of the patient file, depending on ventilation time:

- Apgar and CRIB score
- Ventilation (ventilation route, ventilation type, FiO2.)
- Blood gas analysis (pH, pO2, pCO2, BE, HCO3, SaO2)
- Blood counts (haemoglobin, leukocytes, thrombocytes) clinical chemistry: Na, K, creatinine, urea
- Pathogen detection until 36 week of gestation age
- Weight, head circumference at birth and at day 7-10 and 36 /7 postmenstrual weeks

Additionally, the following materials will be forwarded to the appropriate addresses for testing:

- Cord serum (EPO concentration)
- Continuous NIRS monitoring data before and after first dose for assessment of changes in tissue oxygenation index (only selected infants in Zurich).
- MRI at 40 weeks of gestation (optional)

### **Patient Identification List**

In the CRFs, all patients are anonymised by means of a patient number; to be identified only via the patient identification list. Each centre's patient identification list will be kept exclusively by the investigating physician in the investigating physician's file.

## **Filing of Study Records**

Upon completion of the study, the patient identification list will be filed by the individual investigator for a period of at least 15 years. Likewise, the responsible investigators at the individual study centres will store the Case Report Forms (CRF), as well as the investigator's file containing all pertinent documents, for a minimum period of 15 years after completion of the study.

The trial master file, which is the central file that also contains all pertinent study documents, will be retained by the principal investigator (PI) after the completion of the study for a period of at least 15 years, as will the original findings of the study-specific examinations and the results from the CRFs collated by the monitor.

## **11. Ethical Issues, Data Protection, Quality Assurance, Insurance**

### **ICH/GCP Guidelines, the Helsinki Declaration, Legal Provisions**

The Helsinki Declaration shall be applied to the clinical trial, as well as Good Clinical Practice (GCP) for conducting clinical trials of medicinal products within the European Community, in its current version.

### **Assessment of the Protocol by the Responsible Ethics Committee**

The protocol (version 13 dated 1 June 2005, revised version 15 dated 15 October 2005 and version 16 dated 30 June 2008) have been approved by the Ethics Committee of the Children's Hospital Zurich and the "Kantonale Ethikkommission des Kantons Zürich".

In all further proceedings, the investigator at each participating centre will have to submit the protocol to the respective local Independent Ethics Committee.

### **Handling of Additions/Changes to the Protocol**

With a view to ensuring comparable conditions and faultless data evaluation, changes to the protocol are not planned. In some exceptional cases, however, this could be necessary. Any additions and changes made to the protocol have to be submitted to the appropriate Ethics Committee and authorities for review. Changes to protocol procedures (amendments) require a specification of reasons and must be signed by an authorised signatory for the respective protocol; the amendments are then considered part of the protocol. Substantial changes, in particular with regard to patients' health interests, require a new vote from the Ethics Committee.

### **Information for Parents**

Parents will be given printed information that will be discussed with them.

### **Data Protection Statement**

The written permission for use of the personal and study-related data and passing it on in anonymous form will be obtained before a patient is included. The patients' parents have to give their consent on behalf of their child for this data to be used within a scientific study. If no such consent is given, the data must not be used.

Only those persons involved in the clinical trial will have access to the personal data and to the patient identification list on a need-to-know basis.

## Monitoring, Inspections

Monitoring is employed primarily for the subjects' safety, as well as for quality assurance of medical procedures. The centres will be visited by members of the data safety and monitoring board on a regular basis. Under adherence to the laws on data protection, the investigator's files, data collection forms, and original documents have to be made available to the monitor. The investigators discuss the course of the study with the monitor in appropriate form.

Trial institutions, facilities, laboratories, all data (including raw data) and data collection forms must always be available for inspection by an authority.

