### **Blinding, Packaging, Storage Instructions, Labelling, Shelf Life**

EPO or an equivalent volume of normal saline (NaCl 0,9%) placebo will be administered intravenously before 3 hours, at 12-18 and at 36-42 hours after birth. A single dose consists of 25 µg (3000 IU) human erythropoietin per kilogram body weight dissolved in 1 ml aqua dest. 1 ml per kilogram birth weight (not the actual weight) will be given intravenously within 3 minutes. The maximal dose is 37.5 µg (4500 IU) for infants weighing 1.5 kilograms or more. The packaging, blinding, labelling and storage of the medicine at the pharmacy conforms to the HMG, according to a randomisation list that is only known to the pharmacy.

The individual vials will be allocated unequivocally by their labelling (centre, patient number). Upon request, 1 container per patient will be supplied, allowing 3 days of treatment. Adequate refrigeration (+2 to + 8°C) must be provided during storage at the individual centres, as well as during shipment to the centres. The filled containers have a shelf life of at least 1 week in unopened condition, and are microbiologically innocuous. Unused samples must be stored by the individual centres until the end of the study, and then discarded at the centre in accordance with the monitors' instructions. Disposal of samples must be documented in a disposal protocol (included in the investigator's file).

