## 7.9 Randomisation and Deblinding

The study is randomised on a double-blind basis. This means that the attending investigators do not know whether they are using the placebo or the verum. Randomisation is performed on the basis of randomisation lists (see 4.2).

In the event that deblinding should be required subsequent to an individual patient's withdrawal from the study, this will be possible by immediate notification of the pharmacy responsible for the study centres, with specification of the centre and randomisation number, within 24 hours.

In the event of deblinding, the Principal Investigator has to be notified within a period of 24 hours. The PI will then take charge of further reporting as required by the GCP guidelines.

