## 8. Methods for Assessing Efficacy and Safety

### Appraisal of the Risk-to-Benefit Ratio

In the many EPO trials both in preterm infants and in adults EPO was well tolerated. Adverse effects described in adults are arterial hypertension, polycythaemia, thrombosis and antibody formation against EPO-receptors. As preterm infants tend to have low blood pressure, anaemia and delayed coagulation these side effect of EPO may even be beneficial. Antibody formation occurred in kidney patients after long-term subcutaneous administration of EPO and therefore is very unlikely to be a problem in preterm infants after three intravenous injections. Carcinogenicity finally was observed exclusively in cancer patients who received EPO to treat anaemia, which is hardly relevant for preterm infants.

One retrospective study reports a higher incidence of retinopathy of prematurity in preterm infants treated over 6 weeks with EPO to prevent anaemia compared with controls. This finding could not be confirmed in other prospective randomised controlled trials.

In summary EPO, is considered to be safe. To eliminate the minimal doubts, during this trial infant will be monitored continuously and all adverse events noted and sent to the sponsor at day 10. The safety board will continuously monitor the adverse events and stop the trial if significantly more complications ( $p < 0.01$ ) occur in the verum group.

The nature and extent of the therapeutic interventions employed within the study described here do not go beyond what is therapeutically required for these patients.

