## **Interim Analysis**

After treatment of the first 45 patients, the sponsor will draw up a report on the adverse events and the serious adverse events plus the group sizes, which he will then discuss with the safety board. The report, as well as the minutes of the discussion and any potential consequences from this, will be communicated in writing to all study centres.

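### Site visits are assigned to members of the board that must compare complications by arm, with no firewall, so comparative knowledge can reach blinded investigators

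*Protocol*

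**What the plan says.** Five parts of the protocol bear on this.

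- **Section 11.6 (Monitoring, Inspections)** assigns the visits: "The centres will be visited by members of the data safety and monitoring board on a regular basis". It then makes investigator files, data collection forms and source documents available to the monitor, and adds: "The investigators discuss the course of the study with the monitor in appropriate form".
- **Section 8.1 (Appraisal of the Risk-to-Benefit Ratio)** sets the board's task: "The safety board will continuously monitor the adverse events and stop the trial if significantly more complications", with p < 0.01 as the criterion, "occur in the verum group".
- **Section 7.9 (Randomisation and Deblinding)** defines the blind: "This means that the attending investigators do not know whether they are using the placebo or the verum". Section 6.2 says that the drug is packaged and labelled "according to a randomisation list that is only known to the pharmacy".
- **Section 9.3 (Interim Analysis)** has one report after 45 treated patients: "the sponsor will draw up a report on the adverse events and the serious adverse events plus the group sizes". The sponsor discusses it with the safety board. The report, the minutes of that discussion and any consequences then go in writing to every centre.
- **Section 10.1 (Data Collection Forms)** mentions a monitor in another role: "data entry will be checked by a monitor".

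**The concern.** A board that watches a safety comparison between arms is normally kept apart from the people who enrol, treat and assess patients. Here the protocol sends its members to the centres as routine and sets no limit on what they may discuss there.

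This matters because several outcomes depend on local judgement or local treatment decisions. Under section 7.2, persistent ductus arteriosus is recorded only if it is treated, and necrotising enterocolitis rests partly on clinical signs. Bronchopulmonary dysplasia is defined by oxygen dependency at 36 weeks (section 3.4). Under section 8.5 the investigator judges the severity of each adverse event and its relation to the study drug. An investigator who senses a trend may diagnose, record or attribute differently without intending to. The adverse event records also feed the p < 0.01 rule in section 8.1, so a hint about the comparison could alter the evidence on which the board acts.

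**Working it through.** There is no figure to reproduce, and the point depends on no sample size, power or effect assumption. The check sets the sections side by side.

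1. **Who visits?** Section 11.6 names board members. The only other outside party in that section is an inspecting authority.
2. **Who talks to the investigators?** Section 11.6 says the monitor. Since it names no other visitor, the natural reading is that the visiting board member fills this role, but the section does not say so.
3. **What must the board know?** The rule in section 8.1 is comparative and directional. Pooled event counts cannot show a difference between arms. Coded arms can show a difference, but not whether the excess is on verum. To apply the rule as written, the board, or someone acting for it, must have results by arm and know which arm is which.
4. **Who must not know?** Section 7.9 keeps the attending investigators blind, and they are the people visited.
5. **Is there a barrier between steps 3 and 4?** None is described. No section divides the board into members who see comparative data and members who visit, and none restricts what a visitor may say.
6. **How does this differ from the section 9.3 report?** That report is prepared once, after 45 of 420 infants, which is 45/420 = 10.7% of planned enrolment. Visits are regular, so the route stays open for the remaining 420 − 45 = 375 infants (375/420 = 89.3%), even if the report were kept from the centres.
7. **Is the arrangement needed?** Section 10.1 already mentions a monitor who checks data entry, so a role exists that could take on the visits.

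Steps 1, 3 and 4 together put people whose task requires the comparison in regular contact with people who must not have it. Step 5 shows that nothing in the text prevents its passing on.

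**The case against.** The strongest reply is that the protocol nowhere says that board members see data by arm. The allocation list goes only to the pharmacy (sections 4.2 and 6.2). Deblinding is described only for an individual withdrawn patient (section 7.9). The section 9.3 report lists events and group sizes with no stated split. A separate statistician might run the comparison and tell the board only whether the threshold was crossed, and a board charter could say so. The monitor in section 11.6 may also be a different person, since sections 6.2, 10.1 and 10.4 use the same word for other tasks. The staff list in section 1.1 was not available for checking.

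Much of this stands as a limit on the claim. That the board holds results by arm is an inference from section 8.1. That the safety board and the data safety and monitoring board are one body is reasonable but unstated. The reply does not remove the problem, however. If the board is kept from results by arm, it cannot itself apply the rule in section 8.1. If it has them, section 11.6 sends its members to blinded centres. Either way the sections need to be reconciled. Who visits is also not left open for a charter to settle, because section 11.6 states it.

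A reader might infer more than the text supports:

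- *That comparative results do reach the sites.* The text only leaves a route open.
- *That board members know individual infants' allocations.* No section gives them that.
- *That board members raise data queries knowing the arm.* Section 10.1 describes query forms in the data management software and does not mention the board.
- *That the 24-month Bayley endpoint is biased.* The route described here bears on in-hospital diagnoses and adverse events. Nothing in the protocol links the visits to the developmental assessment.

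**Conclusion.** The point holds as a conflict of roles written into the protocol. Section 11.6 gives regular centre visits to members of the board that, under section 8.1, has to act on a comparison by arm. No safeguard protects the blind described in section 7.9 and in the synopsis row on study design. Comparative knowledge can therefore reach the investigators.

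The exposed data are the in-hospital secondary endpoints that depend on local judgement, and the adverse event records behind the p < 0.01 rule. The size of any bias cannot be computed: the protocol gives neither the frequency of visits nor what visiting members would know or say.

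The conclusion rests on two assumptions: that the two board names refer to one body, and that applying the stopping rule gives at least some members results by arm. The correction should be made, and it is cheap.

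**What to change.** - **Section 11.6:** assign the centre visits to the trial monitor of section 10.1, and state that this monitor has no access to allocation or to results by arm. Add that board members who see comparative data make no monitoring visits, and that they communicate with centres only through a recommendation to continue, modify or stop.
- **Section 9.3:** amend to match, so that no comparative content of the safety report or of the board minutes goes to the centres. Without this, the new text in 11.6 would contradict 9.3, which now sends both documents to every centre.

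The cost is a wording amendment to two sections, submitted to the ethics committee and authorities as section 11.3 requires, and some monitor travel in place of board members' travel. Sample size, endpoints and the stopping threshold are unaffected.

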## Insurance

Insurance is covered by *Haftpflichtversicherung für den Kanton Zürich betreffend das UniversitätsSpital Zürich* (Vertrags-Nr. 8.404.911).

So as not to forfeit their insurance cover, the patients themselves must comply with the following conditions: Any deterioration in the patient's state of health that may have occurred as a result of the clinical trial must be reported immediately to the investigator, so he or she can notify the insurance company. The patient and his or her parents must take any appropriate measures that may help to determine the cause or the extent of damage, and to minimise the damage. In the event of a patient's death, the insurer must be notified immediately. The patient must not be involved in any other clinical trial during the course of this trial, nor within a period of 30 days prior to its beginning or 30 days after its completion.

A copy of the insurance certificate will be placed in the investigating physician's file.

## General Provisions, Agreements, Organisational Procedures

### 12.1 Reports to Authorities

This protocol has been sent to the Federal Institute for Drugs and Medical Devices (Swissmedic) and the study number StV-36/04 has been assigned. Final approval is still pending. Reporting to the appropriate local supervising authorities for each centre will be effected individually by the responsible investigators.

### Final Report

The Final Report for the study will be compiled by the Principal Investigator within a period of 90 days upon completion of the study, and forwarded to the centres, to the Ethics Committees, and to authorities. Furthermore, the sponsor shall undertake to submit the Final Report for publication as soon as possible.

### 12.3 Publications

Publications will be created by the Study Principal (study authors). A report on the primary and secondary endpoints by treatment will be submitted for publication during 2006, an attempt that on refusal will be repeated several times with journals of different impacts. The list of authors will include between one and three treating physicians per centre (depending on the individual requirements of medical journals). The order is defined as follows: 1. Zürich ([name]), 2. investigators of each center in order of number of infants included in the study.

The results of the MRI study will be published separately by [name] and other authors according to their individual contributions.

With regard to publications, the principles of data protection must be observed for patient data as well as for data pertaining to participating physicians.

